### Trial objectives/endpoints

The primary endpoint of this study will be recording of changes of function of the SSN, as assessed by electromyography (EMG) and/or nerve conduction (NC) studies, preoperatively, and at 6 and 12 months postoperatively. All NC/EMG studies, pre and postoperative, will be performed by one neurologist for all included patients. Clinical signs of full recovery will also be assessed and compared pre and postoperatively.

Abnormal function of the SSN in EMG studies will be indicated by fibrillation and high-frequency discharge potentials. An abnormal NC assessment finding is defined according to the following values: infraspinatus latency >4.5 ms and an amplitude <8 mV from peak to peak and supraspinatus muscle latency >3.5 ms and an amplitude <8 mV from peak to peak [12]. The contralateral nerve will also be examined. Abnormal findings are also indicated when the difference in amplitude compared to the healthy side is more than 50%. According to patients’ results, the NC/EMG studies postoperatively will show full recovery of the nerve if all parameters are normal and partial recovery if the tested parameters are improved but not normalized. It is possible, due to some patients’ habitus and size, that NC studies may not be feasible to perform on these patients. In these cases, diagnosis will be established by EMG studies.

The secondary endpoint will be analyzing for possible correlations between tear size, SSN neuropathy frequency, and degree of postoperative nerve recovery. The diameter of the tear will be measured preoperatively with a ruler by using standardized MRI sagittal images. Measurement starts at the insertion of the tendon into the major tuberosity and ends at the most lateral margin of the torn rotator cuff. Only the largest measured diameter of the tear as found on images will be recorded.

The tertiary endpoint will be analyzing the rotator cuff muscles for changes of fatty infiltration as assessed using MRI studies (according to Goutallier’s classification) before and 12 months after the operation [13]. Goutallier classified fatty infiltration as: stage 0, normal muscle; stage 1, some fatty streaks; stage 2, less than 50% fatty muscle atrophy; stage 3, 50% fatty muscle atrophy; stage 4, greater than 50% fatty muscle atrophy.

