### Study population

Forty-two patients with SSN neuropathy and repairable large or massive rotator cuff tears will be recruited according to the inclusion/exclusion criteria of this RCT, divided in two equally numbered groups and treated within a 24-month period at the First Orthopedic Department of Aristotle University of Thessaloniki, “Georgios Papanikolaou” Hospital, Greece. Inclusion criteria are: patients with large or massive repairable rotator cuff tears combined with SSN neuropathy on the ipsilateral side. Exclusion criteria are: SSN neuropathy of another cause (e.g., brachial plexus neuropathy), other previous surgery performed on the same affected shoulder, and moderate to severe degenerative changes to the ipsilateral glenohumeral joint (rotator cuff arthropathy).

All patients seen in our institution’s shoulder clinic with MRI-confirmed large or massive repairable rotator cuff tears and suspected SSN neuropathy will undergo NC/EMG studies in order to establish a diagnosis of the neuropathy. Patients with no signs of pain, atrophy, or paresthesia over the SSN distribution area, or patients who refuse to have any more diagnostic processes, will not have NC/EMG studies and will not be considered for the study. If the above studies are positive for SSN neuropathy, and the patients meet the inclusion and none of the exclusion criteria, they will be informed about this trial. If they agree to participate in this trial and sign and date the informed consent, then a further preoperative appointment will be given.

An investigator will clinically examine the patients on the second preoperative appointment. A specific form will be created for each one that will contain demographic, preoperative, and postoperative data (Additional file 2: Table S1). All patient forms will additionally be kept in electronic records for easier data analysis. Randomization and allocation of patients to a specific group will be done by the statistician. All patients, the clinical preoperative and follow-up examiner, and the neurologist performing the NC/EMG studies will be blinded to the type of surgery performed.

The first group of this trial will be the control group and will consist of 21 patients; these will undergo arthroscopic repair of the rotator cuff tear. The second group will also consist of 21 patients. They will undergo the procedure as above, along with an arthroscopic release of the SSN at the same stage.

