As per the surgical protocol, all patients will also undergo tenotomy of the long head of biceps and acromioplasty with excision of the coracoacromial ligament. Also, excision of the acromioclavicular joint will be performed only if patients complain of pain in that region along with degenerative changes being shown on X-rays, or found intraoperatively. If any further lesions are detected during the operation, the surgeon will proceed to repair them and such incidents will also be recorded. Skin closure will be performed with 3.0 nylon sutures. Nonadhesive dressings and pressure dressings will be applied to the top of the shoulder and patients will be placed in a 30^o^ abduction sling immediately after completion of surgery.

Patients will stay overnight at the hospital. Physiotherapists will advise them as per the physiotherapeutic protocol (Table 2). The abduction sling will remain for the first 6 weeks. Sutures will be removed 10 days after surgery. Outpatient and physiotherapy clinic follow-up will be arranged at 6 weeks, 3 months, and 6 and 12 months postoperatively. Neurology clinics for NC/EMG studies will be arranged at 6 and 12 months postoperatively. Outcome scores will be collected at 6 and 12 months after surgery.

**Table 2 Tab2:** Brief physiotherapy protocol for postoperative rehabilitation of repaired large/massive rotator cuff tears

Time	Focus	Range of motion	Recommended exercises	Precautions
0–6 weeks	Tissue healing	No passive assisted or active ROM of shoulder allowed apart from table slides	• Restricted table slides after 2nd week to 30° • AROM of elbow, wrist, hand	• No active reaching • Sling at all times
6–12 weeks	PROM, AAROM with transition to AROM	Regain full PROM and AAROM, transition to AROM at 10 weeks	• PROM of shoulder, pendulums, scapular mobility, ball squeeze begin AAROM at 8 weeks • Isometrics and active progression at 10 weeks	• No resisted activity and lifting • Avoid overloading of supraspinatus • Must regain scapular rhythm before transition to strengthening
12–24 weeks	AROM and progressive strengthening	Regain full AROM	• Continue PROM and AAROM as needed • Initiate strengthening and progress AROM to functional planes • Progress proprioceptive drills, rhythmic stabilization, push-ups, resistance band	• No heavy or repetitive overhead activities • Limited return to gym after 20th week if AROM with satisfactory scapular rhythm has been achieved • Free full ROM

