## Discussion

Published studies have demonstrated a relation between SSN neuropathy and large/massive retracted rotator cuff tears [8, 9]. Mallon et al. analyzed the outcomes of eight patients with SSN neuropathy and a massive retracted rotator cuff tear. All these patients also presented with SSN neuropathy that was confirmed by EMG studies. Four of these patients underwent partial repair of the cuff. Two of them showed re-innervation potentials [8]. In the Shi et al. study, 87 patients underwent NC/EMG studies and MRI of their symptomatic shoulder. The study concluded that an exact relation between SSN neuropathy and rotator cuff pathology remains unclear and found that SSN neuropathy is associated with tendon tear size. However, this relation was not linear as minimally retracted tears were more strongly correlated with SSN neuropathy when compared to bigger ones. This study aims to better define that relationship and to discover the most effective treatment for this disease. If both interventions performed in this trial have the same potential in reversing SSN neuropathy, then there will be no need to release the SSN when dealing with SSN neuropathy in the setting of large/massive rotator cuff tears. Just by repairing the tendon and, therefore, the length of the muscle/tendon unit, the nerve will be freed and have potential for re-innervation.

Experimental studies have revealed a possible relation between the size of rotator cuff tear and degree of nerve damage. Warner et al., in their cadaveric study, determined that lateral reduction of rotator cuff tears of more than 3 cm might result in significant tension on the SSN and entrapment as the nerve passes through the transverse scapular ligament [19]. Greiner et al., in another cadaveric study, found that that the maximum lateral advancement of a retracted rotator cuff tear is between 1 and 3 cm. As advancement progresses, the neurovascular pedicle is placed under increased tension [20]. However, Hoellrich et al. did EMG studies and did not find any SSN neuropathy after repairs of massive rotator cuff tears in nine patients (mean advancement of 2.5 cm, range 2.0 to 3.5 cm). They concluded that the tendons could be mobilized and advanced up to 3.5 cm without putting the SSN at risk [21]. Although studies suggest nerve damage even after small traction, the medical literature has shifted towards finding a relation between SSN neuropathy and massive rotator cuff tears (more than a 5-cm tendon gap).

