The technique of arthroscopic transverse scapular ligament dissection has been described previously [1, 27–29]. Lafosse et al. in 2007 reported excellent outcomes in nine out of ten patients who underwent SSN arthroscopic decompression without rotator cuff repair [28]. Complete normalization of latency in NC/EMG studies was found in seven of these patients. Costouros et al. reported six patients with SSN neuropathy related to massive cuff tear. He found complete improvement in EMG function in four and partial recovery in two patients [7]. In a study by Shah et al., 21/24 (87.5%) patients had deep posterior shoulder pain and NC/EMG findings of SSN denervation. After SSN decompression, 17/24 (71%) of these patients had reduced levels of pain at 9 weeks after surgery and demonstrated improved ASES scores [30]. The authors also hypothesized that there may be a subgroup of patients with negative NC/EMG studies presenting with unexplained posterior shoulder pain and that these patients may respond to SSN decompression.

The studies above show promising results after release of the SSN, but reversal of muscle atrophy is not always observed. Kim et al. reported 90% of patients with profound muscle weakness regaining supraspinatus muscle strength to grade 4 or better, but infraspinatus muscle strength gains were less predictable [11]. Fabre et al. reported 89% of patients obtaining good-to-excellent outcome after open SSN decompression, but reversal of muscle atrophy was only seen in half of these patients (52%) [31].

In conclusion, published studies so far deliver some evidence regarding the relation between SSN and massive cuff tears and suggest good/excellent postoperative outcomes, with or without releasing the SSN. These cohort studies provide ultimately inconsistent and ambivalent results, as they do not measure their current management with an alternate treatment. The need for comparable studies becomes apparent in order to create a guideline, which would assist shoulder surgeons in making effective and safe treatment choices when dealing with patients with repairable large/massive rotator cuff tears and SSN neuropathy.

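### Equal nerve recovery in two repaired arms cannot show that repair frees the nerve, and the reading that release is unnecessary needs an interval and a named functional score beside it

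*Protocol article*

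**What the plan says.** The Discussion takes the case in which both interventions reverse the neuropathy equally well and draws two conclusions. The first concerns practice: "then there will be no need to release the SSN when dealing with SSN neuropathy in the setting of large/massive rotator cuff tears". The second concerns mechanism: "Just by repairing the tendon and, therefore, the length of the muscle/tendon unit, the nerve will be freed and have potential for re-innervation".

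Under Study population, the control group "will consist of 21 patients; these will undergo arthroscopic repair of the rotator cuff tear". Of the second group it says: "They will undergo the procedure as above, along with an arthroscopic release of the SSN at the same stage". Under Study procedure, "all patients will also undergo tenotomy of the long head of biceps and acromioplasty with excision of the coracoacromial ligament". The same section gives every patient an abduction sling for 6 weeks and one physiotherapy protocol (Table 2).

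Under Trial objectives/endpoints, "The primary endpoint of this study will be recording of changes of function of the SSN", measured by EMG and/or nerve conduction (NC). The secondary endpoint is a set of correlations with tear size, and the tertiary endpoint is fatty infiltration on MRI. The section adds: "Clinical signs of full recovery will also be assessed and compared pre and postoperatively". Constant-Murley, DASH and ASES are scheduled before surgery and at 6 and 12 months (Table 1), but appear at none of the three levels.

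Statistical methods assigns Fisher's exact test to the primary endpoint. The objective is worded as a null hypothesis of equivalent outcomes, and no margin is given.

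**The concern.** The two planned conclusions need different evidence, and the design supplies it unequally.

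The mechanistic conclusion is a causal statement about repair, which every patient receives. If both arms recover alike, that change could come from the repair, another shared procedure, rest, the natural course, or a selected abnormal reading returning towards normal. The comparison between arms cannot separate these.

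The practice conclusion concerns release, which is randomised. Its weakness is that the only planned primary test looks for a difference, in a small sample, with equivalence as the null hypothesis. A non-significant result could easily be reported as sameness. The measure behind it is electrophysiological, and the patient-level scores that could support or temper a recommendation are not named as endpoints.

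At stake is a published statement that repair alone is sufficient, offered towards the treatment guideline that the end of the Discussion calls for.

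**Working it through.** **1. What randomisation separates**

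| Component | Control arm | Second arm |
|---|---|---|
| Cuff repair | yes | yes |
| Biceps tenotomy, acromioplasty | yes | yes |
| Sling for 6 weeks, Table 2 rehabilitation | yes | yes |
| Ligament release | no | yes |

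Only the last row differs. The between-arm difference estimates the effect of adding release to repair. Recovery within an arm is a before-after change with no control.

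The article's own evidence leaves the mechanism open. The Discussion cites a cadaveric study in which lateral reduction of tears over 3 cm might put tension on the nerve, and a nine-patient series with no neuropathy after repair. It also says that a tenotomised muscle affects EMG. A changed EMG after the tendon is reattached is therefore not clearly nerve recovery.

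**2. The plan's own sample size**

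Inputs (Sample size calculation): full recovery 100% with release and 66.67% without, alpha 0.05, power 0.80, ratio 1:1, Fisher's exact test. Sidedness is not stated; two-sided is used here.

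If all 19 release patients recover, the test is significant when at most 14 of 19 controls recover (19/19 v 14/19, p = 0.046; 19/19 v 15/19, p = 0.105). Power is then P(X ≤ 14) for X ~ Binomial(19, 2/3) = 0.812. With 18 per arm it is 0.769. The stated 19 per arm, 38 in total, is reproduced.

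**3. What a non-significant result would mean**

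Power of the same test for a true 20-point difference (the rates are assumptions):

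| True rates | 19 per arm | 21 per arm |
|---|---|---|
| 100% v 80% | 0.327 | 0.414 |
| 90% v 70% | 0.223 | 0.259 |

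At 19 per arm, a 20-point difference is missed in 1 − 0.327 = 67% to 1 − 0.223 = 78% of trials. An observed 19/19 v 15/19, a gap of 4/19 = 21 points, would also be non-significant.

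**4. What identical recovery would leave open**

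Newcombe 95% limits for a difference use the Wilson limits (l, u) of each arm. When both arms have the same proportion p, they are ±√[(p − l)² + (u − p)²]. For 17/19 in each arm, p = 0.895, l = 0.686 and u = 0.971, so the limits are ±√(0.209² + 0.076²) = ±0.222.

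| Observed in each arm | 95% limits (points) |
|---|---|
| 15/19 | ±26 |
| 17/19 | ±22 |
| 19/19 | ±17 |

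**5. For scale: a sample sized against a margin**

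The article gives no margin, so these are assumptions: margin m, equal true rates p, one-sided 0.025, power 0.80. Per arm, n = (1.96 + 0.8416)² × 2p(1 − p)/m².

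- p = 0.6667, m = 0.20: 7.849 × 0.4444/0.04 = 87.2, so 88 per arm, 176 in total.
- p = 0.90, m = 0.20: 7.849 × 0.18/0.04 = 35.3, so 36 per arm, 72 in total.

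Both exceed 38 before any dropout.

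**The case against.** The criticised sentence is conditional, sits in the Discussion, and speaks only of potential for re-innervation. It is not an analysis rule, and the stated primary objective is strictly between arms. That stands: this is a fault of planned interpretation, not of the analysis.

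The article is open about the limits of NC/EMG and says these studies became the reference standard for want of a validated alternative. That justifies the choice of primary endpoint. It does not justify resting a practice statement on that endpoint alone.

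A full protocol or analysis plan may hold a margin or further detail on the scores, and Statistical methods does provide *t* or Mann-Whitney tests for quantitative parameters. That is fair, so a missing analysis description is not the complaint. The point is that the article sets out an explicit endpoint list without the scores, a sample sized for a 33-point difference, and a conclusion that needs more than both.

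Three stronger readings might be inferred, and the documents do not support them.

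- That an unrepaired arm is needed to judge whether release is necessary. It is not: repair versus repair plus release is the correct contrast for that question.
- That there is no functional outcome. Three scores are collected in both arms at baseline, 6 and 12 months, and clinical signs are compared. They are recorded but not ranked.
- That the cited suggestion about pain responding to decompression in patients with negative NC/EMG studies exposes a gap here. It is a hypothesis about patients whom this trial does not enrol, because entry requires positive studies.

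The part played by return of a single abnormal reading towards normal cannot be sized from the article. Entry also requires an MRI-confirmed tear and clinical suspicion of neuropathy.

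**Conclusion.** The point holds in two separate parts. First, the statement that repair itself frees the nerve has no comparator, whatever the sample size. This follows from the arm definitions alone and needs no assumption. Second, the statement that release is unnecessary has the right comparator but weak support. At 19 per arm, identical recovery of 17/19 leaves about ±22 points, and a true 20-point difference is missed in about 67% to 78% of trials. Those figures rest on the recovery rates assumed in the working, on 19 analysed per arm and on a two-sided test.

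The planned primary comparison and its sample size for a 33-point difference are unaffected. What should change is what may be concluded if no difference is found.

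**What to change.** 1. Limit the planned conclusion to the effect of adding release to repair, and label recovery within each arm as descriptive.
2. Report the between-arm difference in full recovery with its 95% confidence interval beside the Fisher test, and state that a non-significant test will not be read as equality.
3. Name one score already collected, for example Constant-Murley at 12 months, as a between-arm secondary endpoint. Require any statement on the need for release to give it, with its confidence interval, beside the NC/EMG result.

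The cost is wording in the endpoint list and the planned conclusion, one more named secondary comparison, and a more modest claim. No new patients, visits or measurements are needed.

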### Trial status

The study is currently in its recruiting phase.

## Abbreviations

ASES: American Shoulder and Elbow Surgeons
CONSORT: Consolidated Standards of Reporting Trials
DASH: Disabilities of the Arm, Shoulder and Hand
EMG: Electromyography
MRI: Magnetic resonance imaging
NC: Nerve conduction
RCT: Randomized controlled trial
ROM: Range of motion
SPIRIT: Standard Protocol Items: Recommendations for Interventional Trials
SSN: Suprascapular nerve
